**Figure 2 F2:**
[figure not shown]
**EBP Checklist**.

At the end of the training, participants will be asked to provide a second set of answers to the Adapted Fresno test and the Questions on attitudes to EBP for post EBP training intervention assessment.

The waitlist control group will undergo the pre and post- knowledge, skills and attitude test at the same period as the intervention group. There will be no training for the control group during this time. However, for the next three months, they will also be provided with activity diaries to log their activities as basis for their treatment when faced with a new or unique case, whether these activities are EBP-related or not.

Three months post EBP training, a third set of answers to the Adapted Fresno test and the Questions on attitudes to EBP, will be obtained from both groups to measure if knowledge, skills and attitudes to EBP were sustained over the three month period in the EBP intervention group and to measure the stability of knowledge, skills and attitudes to EBP of the control group.

### The Intervention

The design of the EBP training program was based on preliminary exploratory studies on the nature and scope of physiotherapy practice in the Philippines, perspectives in teaching EBP to the local physiotherapists and the literature on effective training programs for allied health. From these studies, we identified culture specific strategies to teach Filipino physiotherapists about the concepts of EBP and how to apply them. The most effective training strategies appear to be short and simple lectures with plenty of time for practice sessions [22]. Educational strategies using combined lectures and workshops [26-29] which occur face-to-face and are conducted over at least a half-day are effective to improve knowledge and skills to EBP [22]. Multifaceted interventions and post training support have the potential to improve attitudes and behaviour to EBP, thus a post training online support has been designed for the participants. Principles of adult learning and educational strategies fitted to the type of population have also informed the design of the training program. Adult learners learn more by solving a problem [30] and so we designed the program in a manner where the participants will formulate their own clinical question and at the end of the training, should find an answer to the question based on the lectures and practice sessions provided.

The findings from our preliminary studies and the literature were layered in order to construct the **EBP for FilPTs **training program. The training program is composed of six lectures interspersed with four practical sessions to facilitate learning of knowledge and skills in EBP. The main contents of the training program are:

1. Introduction to EBP

2. Hierarchy of evidence and study designs

3. Drafting the clinical question using the PICO format

4. Designing the search

5. Critical appraisal of the evidence and

6. Answering the clinical question based from the evidence found.

The goal at the end of training is that the clinical question each participant formulated must be answered by the best available evidence. It is anticipated that the best evidence should be identified through a systematic literature search and is appraised as having good methodological quality. Small group discussions will occur during the training sessions to enhance participant learning. The **EBP Checklist **will assist participants to apply the evidence in practice. This will provide the 'tale-home' elements of the training as it can be used by participants to implement the evidence they have found in actual patient cases (Figure 2). This checklist is an innovative concept which physiotherapists who are not first contact practitioners, can use to recommend an evidence-based intervention to doctors for the management of a patient. The EBP checklist consists of items related to applicability or clinical relevance, validity of the evidence base, clinical impact or magnitude of effects. The EBP checklist is comparable to the Relevance, Education, Applicability, Discrimination Evaluation, Reaction (READER) checklist used by general physicians in evaluating the literature to make recommendations for treatment [31]. It is also based partly on the body of evidence matrix of the National Health and Medical Research Council (NHMRC) of Australia [32]. Additional items related to identifying potential barriers to applying the evidence with strategies to address the barriers were also included in this checklist. Barrier and strategy identification in the early stages help facilitate the process of evidence implementation [2].

This EBP checklist will be used by physiotherapists in making recommendations to referring doctors for the treatment intervention. For instance, if there is strong evidence that mobilization decreases pain among patients with chronic neck pain using the pain visual analogue scale (VAS), and the physical therapist has the skills to apply these mobilization techniques, this intervention can be recommended to the referring doctors using the EBP checklist. Mobilization may then form part of recommended treatment procedures, and its effectiveness assessed using a VAS. This process supports the application of principles of EBP, based on research evidence, the physiotherapists' skills and clinical expertise and the patient's goals, within the context of local practice. This process will enhance the decision making skills of the therapists, build their capacity as health professionals and assist them to work with other health professionals in an evidence-based manner.

An EBP online support designed as part of the education model will be made available to participants and can be accessed at this link: http://www.unisa.edu.au/cahe/Resources/EBPPhil/default.asp

The EBP online support allows participants the following:

1. Access the lectures and reference materials from the training (if participants need to review the slides, refresh their knowledge etc)

2. Seek assistance in searching for the evidence to answer their clinical question by filling up the PICO form

3. Seek assistance in validity assessment, through critical appraisal of the evidence found

4. Ask any queries and provide feedback

This follow-up online support complements the training provided to the physiotherapists and is a strategy to address previously identified barriers to evidence-uptake. Multiple strategies and tailored interventions to address barriers are more likely to facilitate changes in behaviour than single interventions [33,34].

### Outcome measures

#### EBP knowledge and skills

The Adapted Fresno Test will be used to measure EBP knowledge and skills. The test was adapted by McCluskey and Bishop [24] from the original Fresno test used in medicine by Ramos et al [35], and has been reported to have acceptable psychometric properties, in measuring change in knowledge and skills to EBP among novice rehabilitation professionals. The test consists of seven questions which address EBP competencies relevant to health practitioners. There are two versions of the test (different clinical scenarios for each test) and ICC scores for subtests were, Version 1: ICC, 0.80-0.96; Version 2: 0.68-0.94 and ICC for total scores were Version 1: ICC, 0.96; Version 2: ICC, 0.91. Internal consistency was acceptable (Cronbach's alpha = 0.74). For our study, version 1 was used for baseline assessment and version 2 for post training assessment. This choice was made to avoid any potential practice effect (defined as "*improvements in cognitive test performance due to repeated evaluation with the same test materials*"). Such practice effects can be a source of error [36].

Inter-tester reliability was assessed among the researchers participating in this study as part of the pilot study of the training program, and acceptable reliability was found (ICC 0.99) for both versions.

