### Plan of analysis

Baseline statistical comparisons will be performed to ensure that all participants from both groups are homogenous and therefore comparable. All post-intervention analyses will be undertaken using an intention to treat approach. Within- and between-group analyses will be undertaken to measure pre and post intervention differences in both intervention and waitlist control group. Changes in outcomes will be compared for both groups using means and 95%Confidence Intervals. Time period for analyses will be pre-intervention, post intervention and three months post intervention.

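### The Adapted Fresno Test version is tied to the time point, so within-arm change cannot be separated from test form and one version must be repeated at three months; the randomised between-arm comparison is not biased by an additive form difference

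*Protocol article*

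**What the plan says.** The subsection on EBP knowledge and skills in the protocol article states: "There are two versions of the test (different clinical scenarios for each test". The order is then fixed for all participants: "version 1 was used for baseline assessment and version 2 for post training assessment". The reason given is: "This choice was made to avoid any potential practice effect". I read this as the rule for the trial, although it is written in the past tense.

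The measurement evidence offered is about reliability: "ICC for total scores were Version 1: ICC, 0.96; Version 2: ICC, 0.91", a Cronbach's alpha of 0.74, and inter-tester agreement of 0.99 for both versions. No mean difference between versions and no equating is reported.

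Under Procedure, the waitlist controls are tested before and after in the same period as the trained arm, without training in between. At three months, "a third set of answers to the Adapted Fresno test and the Questions on attitudes to EBP, will be obtained from both groups". This third test is meant to show whether the trained arm's gains last and, for the waitlist arm, "to measure the stability of knowledge, skills and attitudes to EBP of the control group". The version for the third test is not stated.

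The Plan of analysis commits to both kinds of comparison: "Within- and between-group analyses will be undertaken to measure pre and post intervention differences in both intervention and waitlist control group". It names three time points, and it compares changes using means and 95% confidence intervals.

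**The concern.** From baseline to post training, version and time change together for every participant. If version 2 is easier or harder than version 1, that difference appears in full as change within each arm. Reliability does not settle the matter: two tests can each be scored very consistently and still differ in mean score. No later analysis of these data can separate the two within an arm, because nobody takes version 2 first.

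The affected conclusions are ones the plan intends to draw: the pre/post gain in the trained arm, the stability of controls, and whether gains persist. The controls show the point most clearly. Their first two tests are close together with no training between them, so an apparent change there could be largely a form difference.

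The third test adds a second difficulty. Two versions cannot cover three administrations without a repeat, so the protection against practice that justified switching versions is lost for one of the comparisons. The attitudes questionnaire is not affected, since no alternate forms are described for it.

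**Working it through.** **1. Which within-arm contrasts cross forms.** The first two versions are stated; the third is not, so both possibilities are set out.

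| Contrast within an arm | Third test is version 2 | Third test is version 1 |
|---|---|---|
| Baseline to post | crosses forms (1 to 2) | crosses forms (1 to 2) |
| Post to three months (retention) | same form, practice possible | crosses forms (2 to 1) |
| Baseline to three months (includes control stability) | crosses forms (1 to 2) | same form, practice possible |

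Either way, two of the three contrasts are confounded with form, and the remaining one repeats material already seen.

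**2. Effect on the two kinds of comparison.** Let *d* be the form difference in SD units (version 2 minus version 1), and suppose a true gain of 0.6 SD in the trained arm (the design effect size) and none in controls. The expected baseline-to-post changes are:

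- trained arm: 0.6 + *d*
- control arm: 0 + *d*
- difference between arms: (0.6 + *d*) − *d* = 0.6

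With *d* = +0.3 the trained arm shows 0.9 and controls show 0.3. With *d* = −0.3 they show 0.3 and −0.3. The between-arm difference is 0.6 in both cases.

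**3. Illustrative size for a within-arm test.** The documents give neither *d* nor the pre/post correlation *r*, so both are assumed. The group size of 27 is from the section on sample size determination and is used only as an input. It does not reproduce as a two-sample calculation from the stated 0.6, 80% power and two-sided 5%: 2(1.960 + 0.842)²/0.36 = 43.6, so 44 per group, or 45 with the t distribution. That is a separate matter and does not bear on this point.

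A 95% confidence interval for mean change that excludes zero is equivalent to a paired t-test at 5%. With no true change:

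- SD of change = √(2(1 − *r*)), which is 1.000 at *r* = 0.5 and 0.775 at *r* = 0.7
- noncentrality = *d*/√(2(1 − *r*)) × √27, with 26 degrees of freedom
- example, *d* = 0.3 and *r* = 0.5: 0.3/1.000 × 5.196 = 1.56

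| Assumed *d* (SD) | Significant with no true change, *r* = 0.5 | *r* = 0.7 |
|---|---|---|
| 0 | 5% | 5% |
| 0.1 | 8% | 10% |
| 0.2 | 17% | 25% |
| 0.3 | 32% | 49% |
| 0.5 | 71% | 90% |

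The same probabilities apply to a difference in the other direction, which would appear as decline.

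**The case against.** The strongest reply is that the trial is a randomised comparison with a waitlist control and that this comparison is sound. Controls are tested in the same period with the same form, the plan compares changes between groups, and an additive form difference cancels. This stands. A reader might infer that the effectiveness estimate itself is biased; the documents do not support that. It could be disturbed only if the form difference varied with training, or through a floor or ceiling effect, and nothing in the article points to either.

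Second, a reader might infer that every within-arm contrast is confounded with form. That goes too far: the table shows that one contrast stays within a form, and which one depends on the unstated third version.

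Third, using different forms for the two tests that are close in time and accepting a repeat about three months later is a reasonable use of two forms. The choice of the third form may also be a detail left to a fuller protocol. Both are fair. But whatever that choice is, a repeat cannot be avoided, and the confounding from baseline to post is fixed by the article itself.

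Fourth, it is tempting to say that the version compromises blinded scoring. It shows the scorer the time point, not the arm, and the blinding promised under Randomisation and blinding is to allocation. No breach follows.

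Finally, no actual difference between the versions is shown, and the article describes the test as psychometrically acceptable for measuring change. That is a reason not to presume a large difference, but it is not evidence that the forms are equally difficult.

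**Conclusion.** The point holds for within-arm conclusions only. Baseline-to-post change in each arm is confounded with test form, and at three months either the retention comparison crosses forms and the control comparison from baseline repeats one, or the reverse. The between-arm comparison is unbiased if the form difference is additive. That makes this a moderate-to-minor problem.

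The size is unknown. The range of about 8% to 90% rests entirely on the assumed form difference (0.1 to 0.5 SD), the assumed correlation (0.5 to 0.7) and 27 per group. The upper end should not be read as the expected error rate: at 0.1 to 0.2 SD the figure is 8% to 25%. The point is still worth acting on before the first test, because the fixed order cannot be undone by analysis afterwards.

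**What to change.** - Randomise version order within each arm: about half take version 1 then 2, the rest version 2 then 1 (13 and 14 in a group of 27).
- State the version assignment for three months and balance it within arms. This does not remove the repeat, but it spreads it evenly over versions and arms.
- Include version as a covariate in the analysis of the Adapted Fresno Test.
- Base the conclusions on effectiveness and retention on the baseline-adjusted between-group difference, with its 95% confidence interval, at post training and at three months. Between-group analyses and the three-month time point are already in the plan. Treat within-group changes as descriptive.

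The cost is one more column in the allocation list and one model term. Both versions exist, and inter-tester reliability has been found acceptable on both. The drawback is some added form variance if version is left out of the model. With an even split it adds *d*²/4 to the score variance at a single time point, for example 0.3²/4 = 0.0225 against a score variance of 1. It adds more to raw change scores, where the two orders shift by +*d* and −*d* and so contribute *d*² = 0.09. The covariate should therefore be specified in advance.

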#### Questions to EBP attitudes

The Questions to EBP attitudes [25] will be used to assess the attitudes domain of EBP in this study. The attitudes to EBP scale consists of seven questions which are answered using a 3-point Likert scale: agree, neither agree nor disagree and disagree. The scale has been developed and validated for content and ease of completion [25]. In addition to this, participants will provide their comments on EBP and the EBP training program as part of this assessment.

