#### Randomisation and blinding

An independent researcher will randomly allocate participants into either the EBP training group or a waitlist control group, using a computer generated random numbers. Allocation into treatment and control groups will be undertaken by an independent research assistant who is unaware of the study objectives and the participants. The schedule of training will depend on the group allocation, such that those in the intervention group will have their training earlier than the waitlisted control group. Participants and assessors of the study outcomes will be blinded to the allocation at all times.

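### Comments on the training programme, collected within the attitude assessment, reveal the arm to any assessor who reads them, which conflicts with the promise of blinded assessors

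*Protocol article*

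**What the plan says.** All references are to the protocol article.

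- **Questions to EBP attitudes.** The scale has "seven questions which are answered using a 3-point Likert scale: agree, neither agree nor disagree and disagree". The section then adds that "participants will provide their comments on EBP and the EBP training program as part of this assessment". It does not restrict this to one arm or to one time point.
- **Procedure.** The AFT and the attitude questions are administered together on three occasions. The baseline set is emailed to all participants the day before the intervention group's training. After training, "The waitlist control group will undergo the pre and post- knowledge, skills and attitude test at the same period as the intervention group". Of the controls in that interval it says: "There will be no training for the control group during this time". At three months, "a third set of answers to the Adapted Fresno test and the Questions on attitudes to EBP, will be obtained from both groups", and for controls the stated purpose is to measure stability.
- **Randomisation and blinding.** "Participants and assessors of the study outcomes will be blinded to the allocation at all times".
- **EBP knowledge and skills.** "Inter-tester reliability was assessed among the researchers participating in this study" in the pilot, with an ICC of 0.99 for both versions of the AFT.
- **Plan of analysis.** Changes in outcomes are compared by means and 95% confidence intervals. No use or scoring of the comments is mentioned.

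**The concern.** An outcome assessment should look the same in both arms to the person who processes it. Here one component can be answered meaningfully in one arm only. A participant who remarks on the lectures or the practical sessions has disclosed the allocation, and the article promises that assessors will not know it.

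This matters because assessor blinding is the protection that can realistically be kept in this design. Participants know whether they have attended a training day, whatever the blinding statement says. The AFT is the outcome on which a marker's judgement can act. If markers learn the arm, its between-group difference is open to marking bias.

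**Working it through.** The point depends on no sample size, power or effect size, so there is nothing to recompute. It is settled by setting the sections side by side.

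1. **Who could comment on the course, and when?** This follows from the schedule under Procedure.

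| Assessment | Trained arm | Waitlist arm |
|---|---|---|
| Baseline, day before training | Not yet trained | Not yet trained |
| After training | Trained | Untrained |
| Three months | Trained | Untrained |

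The three-month entry for controls is inferred: the article uses that assessment to measure the stability of their knowledge, skills and attitudes, which makes sense only if they are still untrained. A substantive course comment is therefore possible at 2 of 3 assessments in the trained arm and at 0 of 3 in the control arm. The article does not say at which assessments comments are requested, so 2 of 3 is an upper limit. Controls can still comment on EBP in general; it is the course comment that gives the arm away.

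2. **Is this compatible with the blinding statement?** The comments are defined as part of an outcome assessment, and assessors of the outcomes are to be blinded throughout. Anyone who reads that assessment in full, as defined, can learn the allocation of those who commented on the course. Both statements can be true only if the comments are kept from the assessors, and the article states no such step.

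3. **Which outcome could be affected?**
   - *Attitude items.* They are closed, have three response options and are self-completed. A processor who knows the arm has little room to change the score.
   - *AFT.* Testing agreement between raters makes sense only if raters mark the test, and the raters named are researchers in this study. Marker knowledge could act here. The article does not say who marks in the trial itself, or whether those markers also receive the attitude assessment.

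4. **Do the comments enter the attitude score?** Nothing indicates it. The comments are introduced with "In addition to this, participants will provide their comments on EBP", which sets them beside the seven items, and the Plan of analysis gives them no role.

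5. **Does the pilot ICC of 0.99 remove the concern?** No. It shows that raters agreed with one another. Markers who share knowledge of the arm can agree closely and still be biased in the same direction. Equally, it is no evidence that such a bias exists.

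**The case against.** The strongest reply is that the article names two separate tools and nowhere says that AFT markers receive the attitude assessment or the comments. It commits to blinded assessors, and how papers are coded, separated and routed is the kind of detail an article leaves to the full protocol. The comments may also be no more than ordinary course feedback from trainees, such as the pilot participants gave.

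Much of this stands, and it rules out three stronger readings.

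- *That the markers are unblinded.* A reader might infer this, but the article does not say that they see the comments. It is a conditional risk.
- *That course feedback contaminates the attitude measure.* The two are collected together, but no section combines them in a score.
- *That the comment request biases attitude answers in one arm through courtesy.* Trained participants complete the items at the end of the training day and know they were trained, with or without a comment request. Any such pressure is largely independent of it, and removing the request would leave most of it in place.

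What the reply does not remove is the conflict in the stated text. The point does not rest on missing routing detail: the article affirmatively places arm-revealing content inside an assessment whose assessors it says are blinded, and does not limit the request to trainees or separate it from the outcome forms.

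**Conclusion.** The point holds as a conflict between a stated procedure and a stated blinding property. Course comments gathered within the attitude assessment reveal the arm to any assessor who reads them. The exposed outcome is the AFT.

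This rests on two assumptions: that study researchers mark the AFT in the trial, which the pilot reliability work suggests but does not state; and that those markers could see the comments, which the article neither states nor excludes. If the second fails, AFT marking is unaffected.

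The size of any bias cannot be derived from the document, and any figure for a marking shift would be a guess. The case for acting is that the conflict is plain and the repair is small.

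**What to change.** 1. Give both arms an identical attitude form, without comments on the training programme, at all three time points.
2. Collect course feedback from trained participants only, on a separate sheet handed out after the AFT and attitude forms have been returned.
3. Keep that sheet from AFT markers until marking is complete.
4. Identify AFT scripts by code only.
5. State that comments do not enter the attitude score.

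The only cost is handling one extra form. No data are lost, and no additional participants or assessments are needed.
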